### Measures

#### Primary outcome measure

The primary outcome measure will be change in psychosocial functioning as measured by total score on the HoNOS [37]. It is hypothesised that there will be no significant difference in the mean change in highest total HoNOS score recorded in the 0–12 months prior to CCU commencement and the highest score recorded 0–12 months post CCU discharge for consumers under the clinical and integrated staffing model. The total HoNOS score has been selected as the primary outcome measure as it:Has high validity, reliability and sensitivity to change, as well as routinely informing service policy and planning decisions in Australia [38];Is considered appropriate for tracking changes in social functioning over time, and more sensitive in doing so than the CANSAS (a needs based measure) [39];Has an embedded role in individual outcome assessment in Australia and New Zealand [38, 40, 41] and there is evidence that it is being regularly utilised in care planning [42, 43]Is supported by an established national assessment protocol and training processes to facilitate inter-rater reliability [38], and with evidence to support higher levels of acceptability [44] and completion than the other core measures of routine outcome suite [38]It is used and available across multiple international settings [45], increasing the replicability of the methodology.

Utilising the criterion of the highest (i.e. greatest dysfunction) score in the 12-month period pre and post CCU entry limits the risk of conflating the benefits of active rehabilitation support with the benefits associated with support and accommodation in the CCU setting.

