### Quantitative methodology

#### Design

A longitudinal, prospective cohort design is used to examine outcomes of consumers under the clinical and integrated staffing models. The methodology has been developed with consideration of the STROBE Statement [33] and it is intended that results will be reported in a manner consistent with these guidelines. Principles of relevance to the quality reporting of equivalence studies have also been considered [34]. Prospective data will be obtained from a clinical assessment battery at three time points: admission, discharge and the 0–12 months post-discharge (see Table 2). Supplementary data will also be available retrospectively for the period 0–12 months prior to CCU admission from routine administrative data sets.

**Table 2 Tab2:** Routine clinical assessment battery and administrative data collection over the baseline, admission, discharge and follow-up collection points

Domain		Measure	Baseline (−12–0 months)	Admission (0–6 weeks post)	Discharge (0–6 weeks prior)	Follow-up (0–12 months)
Administrative data		Health of the Nation Outcome Scale (HoNOS) [26]^A^	X	X	X	X^1^
		Life Skills Profile (LSP-16) [48]^B^	X^*^	X	X	X^2^
		Mental Health Inventory (MHI-38) [51]^B^	X	X	X	X^2^
		Mental health related Emergency Department presentations	X	X	X	X^2^
		Psychiatric inpatient bed days	X^*^	X	X	X^2^
Clinical assessment battery	Symptom measures	Alcohol Use Disorders Identification Test (AUDIT) [60]		X^*^	X	
		Brief Psychiatric Rating Scale (BPRS) [46]		X	X^2^	
		Scale for the Assessment of Negative Symptoms (SANS) [87]		X	X^2^	
	Functional Cognition	Allen’s Cognitive Levels (ACL) [59]		X^*^	X	
	Social-function	Social Functioning Scale (SFS) [88]		X^*^	X^2^	
	Functional	Perceive Recall Plan & Perform System of Task Analysis (PRPP) [89]		X	X	
	Recovery	Stages of Recovery Instrument (STORI-30) [49]		X^*^	X^2^	
	Carer burden	Burden Assessment Scale (BAS) [90]		X	X	
		Adult Carer Quality of Life (AC-QoL) [50]		X	X^2^	

^A^ HoNOS is routinely collected on admission and discharge from inpatient, community residential and ambulatory services, and 3-monthly review periods in the non-inpatient settings

^B^ LSP-16 and MHI are routinely collected on admission, discharge and 3-monthly review in community residential and ambulatory services

^1^ Primary outcome measure, examining change in total score between the Baseline and Follow-up periods

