### Sample

The project is currently in progress. The cohort will comprise all consumers admitted to the three MSAMHS CCUs (Bayside, Coorparoo and Logan) between December 2014 and December 2017 who provide informed consent to participate. Baseline and follow-up data will be sourced from administrative datasets for the 12-month period prior to and following CCU admission and discharge respectively.

As the study takes a naturalistic observational design, the only defined inclusion criteria is acceptance for a trial of CCU based rehabilitation care. Each CCU provides a six-week assessment period to establish suitability for engagement under the model of service. Given this, consumers who are discharged prior to the conclusion of this assessment period will be excluded from the study. This exclusion criterion assists in ensuring that included participants are aligned with the model of service. This reflects a modified intention-to-treat approach [34], as participants will be included regardless of their mode of exit from the CCU (planned/unplanned (CCU initiated)/unplanned (consumer initiated).

Based on anticipated service throughput, with a median length of stay at the Coorparoo CCU of 0.9 years (inter-quartile range 0.50-1.8 years) at a point estimate in 2013, and assuming a 70 % response rate, it was expected that at least 60 consumers from the integrated staffing model and 40 from the clinical staffing model would agree to participate over the study period. This minimum sample likely reflects an under-estimate given 37 unique admissions occurred to the Coorparoo CCU in the 12-month period from July 2012. Additionally, since the opening of the Bayside and Logan CCUs 50 of the 63 consumers admitted across all three sites met the inclusion criteria (79.4 %) and 42 (84.0 %) of eligible consumers provided consent to participate.

The adequacy of the estimated minimum sample size was considered using the Epi Info™ StatCalc program [35] for unmatched or cross-sectional cohort studies. This minimum sample was estimated to provide greater than 80 % power to detect a 15 % difference in outcome on the primary outcome measure at the 95 % confidence interval using the Fleiss calculation. The acceptability of this power is supported by an emergent difference of 20 % in outcome HoNOS scores in a recent Australian study examining outcomes of a community residential service for similar consumers [36].

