### Procedures

Identical processes for data collection will operate at the three sites. The clinical assessment incorporates a combination of clinician, consumer, clinician-and-consumer and carer/family completed measures (see Table 2). For the purposes of this study a Carer is considered to be a person (e.g. family member or friend) who the Consumer nominates as having a significant unpaid caring role for them. Staff for which each measure reflects their core-skills set and routine practice will be responsible for measure completion (see Table 3).

The research protocol was explained to staff prior to the commencement of data collection. Each discipline completing relevant assessments will work to maximise fidelity through regular peer based supervision. Standardised training in the use of routine outcome measures is provided to all staff, this includes opportunities to calibrate scoring of HoNOS and Life Skills Profile-16 (LSP) [48] across the study sites. Fidelity of data relating to symptom measures will be enhanced through the use of the anchored scoring version of the Brief Psychiatric Rating Scale (BPRS-A) [62] and a semi-structured interview guide developed in an Australian context for raters with low-clinical experience [63], as well as a structured interview guide for the Scale for the Assessment of Negative Symptoms (SANS) measure [64]. Inter-rater reliability data will also be calculated from calibration sessions for the BPRS and SANS involving relevant staff.

A research assistant will collate the data from the pre-admission and post-discharge phases from established administrative data sets, where the relevant information is routinely collected.

As is commonly expected in health research [65, 66], it is anticipated that missing data will be present in both the administrative datasets and assessment battery. Categorical codes will be available for non-completed consumer and carer measures, and for clinician rated measures dependent on structured assessment. These codes will designate the reason for non-completion as being due to refusal by the consumer/carer or due to the measure not being offered to the consumer/carer. Missing Values Analysis will be completed in SPSS Version 22 and it is planned for missing data to be handled using the multiple imputation method [67] assuming this is missing at random. Characteristics and patterns of missing data, and the assumed mechanisms will be reported.

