There are inherent limitations with relying on routinely collected administrative and clinical data, including missing data and recording bias [36]. Furthermore, the absence of blinding of raters provides a potential source of bias, however the primary outcome assessments in during the baseline and discharge periods will be completed by trained assessors independent of the CCU context. The absence of randomized allocation between the staffing models hinders our ability to make causal inferences regarding relationships between service provision and changes in outcome over time. However, the inappropriateness of running randomized placebo-controlled trials in socially complex services with reference to ethical and practical barriers has been acknowledged in the literature [30]. Regardless, the utility of equivalence testing depends in part on the underlying assumption that the comparator has been convincingly proven to have superior efficacy to placebo [77]. This assumption cannot be definitively asserted on the basis of the available literature.

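### The primary outcome subtracts one highest routine HoNOS rating from another, so unequal numbers of ratings between staffing models could create or hide a difference

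*Protocol article*

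**What the plan says.** Protocol article, 'Primary outcome measure': the two models are compared on mean change between the "highest total HoNOS score recorded in the 0–12 months prior to CCU commencement and the highest score recorded 0–12 months post CCU discharge". The reason given for using the peak begins "Utilising the criterion of the highest (i.e. greatest dysfunction) score in the 12-month period pre and post CCU entry limits the risk"; in full, the claim is that the peak "limits the risk of conflating the benefits of active rehabilitation support with the benefits associated with support and accommodation in the CCU setting". The number of ratings that feed each peak is not discussed there.

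The same article, 'Sample', gives the source: "Baseline and follow-up data will be sourced from administrative datasets for the 12-month period prior to and following CCU admission and discharge respectively". The occasions for rating are in 'Design', Table 2, note A: "HoNOS is routinely collected on admission and discharge from inpatient, community residential and ambulatory services, and 3-monthly review periods in the non-inpatient settings".

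'Analysis' compares the models on this change with a t-test or a Mann–Whitney U test at the 0.05 level. 'Aims and benefits' states the expectation as no significant difference between models. For gaps in the data, 'Procedures' says "it is planned for missing data to be handled using the multiple imputation method [67] assuming this is missing at random", with patterns and assumed mechanisms to be reported. 'Discussion' concedes in general terms: "There are inherent limitations with relying on routinely collected administrative and clinical data, including missing data and recording bias".

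**The concern.** The highest of several noisy ratings lies above the person's own average level, and further above it the more ratings there are. Note A makes the number depend on the care received. Non-inpatient contact brings a review every three months. An inpatient stay brings only an admission and a discharge rating. An episode closed early leaves few ratings, and a year without contact leaves none.

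Staffing model cannot be separated from district, because the clinical model runs at one unit and the integrated model at two others. In Table 1 ('Evaluation context'), inpatient rehabilitation beds exist only in the Bayside district, a transitional housing team only in Coorparoo's, and a non-residential rehabilitation team in Coorparoo's and Logan's but not Bayside's. 'Discussion' itself expects referral patterns to differ by site. Equal rating counts under the two models therefore cannot be taken for granted.

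The hypothesis is that no difference will emerge. An imbalance in counts can produce a spurious difference, but it can also cancel a real one and so appear to confirm the hypothesis.

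**Working it through.** The plan gives no rating counts and no HoNOS standard deviation, so it has no figure of its own to reproduce on this point. The check shows what a given imbalance would do.

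**Inputs from the protocol.** Maximum minus maximum ('Primary outcome measure'); 40 clinical and 60 integrated consumers ('Sample'); t-test at 0.05 ('Analysis', taken as two-sided).

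**Assumptions, not in the protocol.** Normal ratings; within-person SD σ = 4 (range 3 to 5); between-person SD 5; four pre-admission ratings per person under both models; no true difference. Ratings are either independent, or correlated 0.6 at three months and spread evenly over the window.

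**Step 1: plausible counts.** Continuous ambulatory contact gives 12/3 = 4 reviews, so about 4 to 5 ratings with one at opening or closure. Each inpatient episode adds about 2. Early closure leaves 1 or 2.

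**Step 2: expected excess of the maximum.** For k independent ratings, in within-person SDs, m(k) = ∫ x·k·φ(x)·Φ(x)^(k−1) dx. This gives m(1) = 0, m(2) = 0.564, m(4) = 1.029, m(5) = 1.163, m(6) = 1.267 and m(8) = 1.424. With the correlation above, simulation gives 0.45, 0.75, 0.82 and 0.87 for k = 2, 4, 5 and 6.

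**Step 3: shift between models.** The spurious difference in mean change is σ × {[m(post, A) − m(pre, A)] − [m(post, B) − m(pre, B)]}. With equal pre-admission counts this is σ × [m(post, A) − m(post, B)]. Under independence:
- 5 vs 4: 4 × (1.163 − 1.029) = 0.54 points (0.40 to 0.67 for σ of 3 to 5)
- 6 vs 4: 4 × (1.267 − 1.029) = 0.95 (0.71 to 1.19)
- 4 vs 2: 4 × (1.029 − 0.564) = 1.86 (1.40 to 2.33)
- only 20% of one arm with 8 instead of 4: 0.20 × 4 × (1.424 − 1.029) = 0.32 (0.24 to 0.39)

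**Step 4: rejection rate with no true difference (simulated, 40 vs 60, σ = 4).** Ranges show the spread between simulation runs.

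| Post-discharge ratings | Independent: shift, rejection | Correlated: shift, rejection |
|---|---|---|
| 4 vs 4 | 0, 5% | 0, 5% |
| 5 vs 4 | 0.5, 9–11% | 0.3, 6% |
| 6 vs 4 | 1.0, 22% | 0.5, 8–9% |
| 4 vs 2 | 1.9, 57–58% | 1.2, 22–23% |

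When the mean of the ratings replaces the maximum, rejection stays at about 4 to 6% in every row.

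**Step 5: masking.** Let the integrated arm be truly 2 points worse after discharge, with 2 ratings against 4. Under independence the observed difference falls from 2.0 to 0.1 points and rejection from 70% to 5%. With the correlation it falls from 2.0 to 0.8 points and rejection from 52% to 13%.

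**Step 6: existing safeguards.** National assessment protocols, training and calibration of scoring address consistency between raters, not how often a consumer is rated. Multiple imputation addresses consumers with no rating. A consumer with one or two ratings has a maximum that counts as fully observed.

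**The case against.** The case for leaving the plan alone has real parts.

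- **The peak is deliberate and partly signal.** A rating triggered by relapse records the deterioration a peak score is meant to capture, so not all dependence on contact is artefact. This stands, and it is why the highest score can remain primary.
- **No imbalance is shown.** Acute inpatient and community mental health services exist in all three districts, and the units share governance and a model of service. This also stands. The documents establish that an imbalance is possible, not that it exists.
- **Independence exaggerates.** Serial correlation shrinks the figures, as the table shows, but does not remove them.
- **Details belong in an analysis plan.** That is true of imputation models and count tables. The endpoint definition and the primary test, however, are fixed in the article.

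A reader might also infer more than the documents support:

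- That taking the worst score builds improvement into the result. The maximum is taken in both windows, so with equal counts the two excesses cancel. Admission at a bad time could still cause regression to the mean, but it would do so for a mean score too, and it affects the comparison of models only if it differs between them.
- That a shift of 1.2 to 3.0 points is the bias. That is what one person gains by moving from 4 to 8 or from 2 to 5 independent ratings with σ of 3 to 5. It is not a difference between arms.
- That the outcome vanishes when contact ends. Someone who leaves services part-way through the year still has a maximum, from fewer ratings.
- That imputation overstates the dysfunction of consumers without contact. They could be better or worse than those still in care, and nothing in the protocol settles the direction.

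**Conclusion.** The concern holds as a weakness in the design of the primary outcome, and it is worth correcting. As defined, the endpoint depends on how often each consumer happens to be rated. That frequency depends on services that differ in part between districts, and the primary test does nothing about it.

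Size and direction are unknown without the counts. Under the stated assumptions the effect runs from small (one extra post-discharge rating per person: about 0.3 to 0.5 points, 6 to 11% rejection) to serious (4 versus 2: about 1.2 to 1.9 points, 22 to 58%). It can hide a difference as well as create one. The documents do not support a claim that the comparison is biased, only that it is unprotected.

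The phrase post CCU entry, in the rationale, might suggest that the second window covers the stay in the unit. It is a slip of wording: the definition in the same section and the 'Sample' section both place that window after discharge.

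**What to change.** 1. Keep change in the highest score as the primary outcome. Pre-specify a supportive analysis of change in the time-weighted mean of all ratings in each 12-month window, from the same records.
2. Tabulate the number and setting of ratings per window, by staffing model.
3. State in advance that the equivalence conclusion will be tempered if the two analyses disagree.
4. For consumers with no post-discharge rating, add a delta-adjusted sensitivity analysis to the missing-at-random imputation, in both directions (imputed HoNOS shifted lower and shifted higher).
5. Align the words post CCU entry in the rationale with the post-discharge definition.

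The cost is a second extraction and one further analysis, with no new data collection. The mean is imprecise when a consumer has only one or two ratings, and it does not remove dependence on the setting in which ratings are made; the table in item 2 makes that dependence visible. If the results diverge, the conclusion will be more cautious.

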### Planned secondary outcome measures and descriptive data

The complexity of outcome assessment in mental health service evaluation and the appropriateness of relying on multiple measures to capture the breadth of relevant domains is well recognised [45]. A routine assessment battery (see Tables 2 & 3) was developed, piloted and adapted at the Coorparoo CCU site in consultation with senior medical and allied health workers over the initial two years of operation (2012–2014). Considerations in the development of this battery included ease of administration, incorporation of multiple perspectives (staff, consumers and carers) and sufficient breadth to capture data on functional, social, cognitive, recovery and symptom related domains.

**Table 3 Tab3:** Completion of relevant measures and explanation of routine clinical assessment battery

		Responsible person for ensuring completion					
Domain	Measure	Occupational therapist	Principle service provider	Psychology`	Medical	Social work	Notes on assessment battery
Routine outcomes	Life Skills Profile (LSP-16)^a^		X				•These measures form part of the routine assessment battery to be completed with all consumers residing at the Community Care Units. •The battery was developed on the basis of the clinical experience and knowledge at the Coorparoo CCU, with extensive staff consultation. •Standardisation of the assessment process provides an opportunity to better evaluate and compare consumer outcomes, both at the individual and group level. •Whilst there many other relevant measures, the battery chosen aims to broadly cover relevant domains in a manner that does not place excessive demands on consumers, carers and staff. •There will not be an opportunity to change the components of the battery for the duration of the CCU evaluation project. For this reason, it will be critical to find ways in which the chosen measures can be utilised to enhance the quality and experience of care at the units. •It is expected that the measures completed by carers and consumers will form the basis of a subsequent discussion with members of the clinical team. •It is likely that multiple team members may be present at the time a given measure is collected given the multi-disciplinary nature of the work undertaken at the CCUs. •The Principle Service Provider role under both the integrated and clinical staffing models is performed only by clinical staff members. •For the purposes of this study a Carer is considered to be a person (e.g. family member or friend) who the Consumer nominates as having a significant unpaid caring role for them.
	Mental Health Inventory (MHI)^b^		X				
	Health of the Nation Outcome Scale (HoNOS)^a^		X				
Symptom measures	Alcohol Use Disorders Identification Test (AUDIT)^c^				X		
	Brief Psychiatric Rating Scale (BPRS)^d^			X			
	Scale for the Assessment of Negative Symptoms (SANS)^d^				X		
Cognitive	Allen’s Cognitive Levels (ACL)^d^	X					
Social	Social Functioning Scale (SFS)^c^	X					
Functional	Perceive Recall Plan & Perform System of Task Analysis (PRPP)^d^	X					
Recovery	Stages of Recovery Instrument (STORI-30)^b^		X				
Carer burden	Burden Assessment Scale (BAS)^b^					X	
	Adult Carer Quality of Life (AC-QoL)^b^					X	

^a^ Clinician rated measure

^b^ Consumer / carer self-rated measures

^c^ Consumer / carer self-rated measures with the option of oral administration by a staff member

^d^ Clinician rated measure based on interview / assessment with consumer

X Collection occasion

Planned secondary outcome measures will be derived from this assessment battery and routine administrative data sets. Secondary outcome assessment will specifically focus on mean changes in symptomatology (Brief Psychiatric Rating Scale (BPRS) [46] & Scale for the Assessment of Negative Symptoms (SANS) [47]), disability (Life Skills Profile-16 [48]), recovery orientation (Stages of Recovery Instrument (STORI-30) [49]), carer quality of life (Adult Carer Quality of Life (AC-QoL) [50]), emergency department presentations, psychiatric inpatient bed days, and psychological distress and wellbeing (MHI-38) [51]). For each of these secondary measures it is again hypothesised that no differences in mean change will emerge between the clinical and integrated staffing models.

Descriptive details of consumer characteristics and care experience will also be recorded. Relevant information will include: age at CCU commencement, gender, ethnicity, marital status, years of education, diagnosis, involuntary treatment order status, medication, length of stay, and the mode of exit from the CCU (planned/unplanned (consumer initiated)/unplanned CCU initiated).

Information about the operational costs under the integrated and clinical staffing models over the December 2014 - December 2017 period will be reported descriptively. Additional information about the operational experience under the integrated and clinical staffing models including staff retention and absences will also be reported. Estimates of the cost of ongoing service utilisation following CCU engagement based on ED Presentations and acute inpatient bed days in the 12-months post-CCU discharge will be calculated using the most recently available state-wide cost estimates.

